## 2. Materials and Methods

### 2.1. Study Design

This is a prospective cohort study aimed at validating the effectiveness of two novel non-invasive imaging biomarkers. It will be conducted at Sant Joan de Déu Hospital, a tertiary children’s hospital in Barcelona (Spain). The recruitment and follow-up period is planned from June 2025 to June 2027. As previously mentioned, the imaging acquisition protocol will guide the various phases of the study (Figure 2):

Phase 1: Measurement of elastance and microvascularization ratio in well-aerated (non-consolidated) lung tissue. Patients without pulmonary consolidation will be included in this phase.

Phase 2: Measurement of elastance and microvascularization ratio in consolidated lung tissue. Patients with confirmed pulmonary consolidation via LUS (even if the initial detection was through other imaging techniques) will be recruited. Patients will then be classified into two groups based on the final diagnosis:Group 1: BPGroup 2: Atelectasis

The final BP diagnosis will be made by a clinical expert using the BTS definition for CAP and the CDC criteria for VAP. This includes compatible clinical symptoms (such as fever, cough, tachypnea, and shortness of breath), abnormal auscultation patterns, LUS findings (according to Section 2.4.1), and blood test abnormalities suggestive of bacterial infection (leukocytosis, neutrophilia, CRP > 50 mg/L, and/or PCT > 1 ng/mL). Atelectasis will be diagnosed in patients with respiratory distress, without blood test abnormalities suggestive of bacterial infection (CRP < 50 mg/L and PCT < 1 ng/mL), and compatible LUS findings (according to Section 2.4.1), which resolve after increasing ventilatory support and performing respiratory physiotherapy.

For the differential diagnosis of both entities, respiratory sample cultures will not be considered, as false negatives may occur (in the context of BP) or colonizing organisms may be detected (even in cases of atelectasis).

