## 1. Introduction

Acute lower respiratory tract infections are highly prevalent in the paediatric population and represent one of the leading causes of admission to paediatric intensive care units (PICUs) [1]. Specifically, community-acquired pneumonia (CAP) remains one of the primary causes of death among paediatric patients worldwide [2]. The typical symptoms of pneumonia are fever, cough, tachypnoea, and respiratory distress. However, younger children may present with non-specific symptoms such as irritability or refusal to feed [3]. CAP is primarily caused by bacterial or viral infections. Although the diagnosis of CAP generally relies on a combination of clinical signs, blood tests, imaging techniques, and microbiological parameters, the British Thoracic Society (BTS) recommends basing the diagnosis on clinical findings alone, advising against routine use of chest X-rays (CXRs) to reduce radiation exposure. Furthermore, the use of acute phase reactants to differentiate between viral and bacterial infections is discouraged [4]. In the PICU setting, nosocomial pneumonia (NP) due to bacterial infection is particularly common. This category includes both hospital-acquired pneumonia and ventilator-associated pneumonia (VAP) and constitutes one of the main healthcare-associated infections in hospitals [5]. NP should be suspected in any patient who develops a lung infection after 48 h of hospitalization or within the first 7 days following hospital discharge. Focusing on VAP, it develops after 48 h of mechanical ventilation and is identified by the presence of a new infiltrate on CXR, along with positive microbiological findings from the lower respiratory tract and/or two or more positive clinical signs of pneumonia. VAP is a highly prevalent condition, and while there is no single Gold Standard diagnostic tool, the Centers for Disease Control and Prevention (CDC) criteria are the most widely accepted and utilized [6].

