**Figure 4 diagnostics-15-00910-f004:**
[figure not shown]
Presentation interface of the SMI mode on the Aplio A500 device (Canon™).

**Table 1 diagnostics-15-00910-t001:** Comparison of the characteristics of CXR, LUS, SWE, and SMI for the evaluation of pulmonary pathology.

	CXR	LUS	SWE	SMI
**Irradiation**	Yes	No	No	No
**Bedside**	No	Yes	Yes	Yes
**Reproducibility**	Not operator-dependent	Operator-dependent	Operator-dependent	Operator-dependent
**Quantitative data**	No	No	Yes	Yes
**Type of information it provides**	Anatomy overview and possible pulmonary pathologies	Pleural effusions, pneumothorax, or superficial lung consolidations	Elasticity of the lung tissue	Lung microvascularization, (perfusion and small blood vessels)

CXR: Chest X-Ray; LUS: Lung Ultrasound; SWE: Shear Wave Elastography; SMI: Superb Microvascular Imaging.

**Table 2 diagnostics-15-00910-t002:** Set of variables to be collected during the study.

	Variables
**Anthropometric and Demographic**	- Age - Sex - Weight - Ethnicity
**Clinical and analytical**	- Reason for admission to PICU (if admitted) - Heart rate, respiratory rate, blood pressure and oxygen transcutaneous saturation and pulmonary auscultation findings. - Presence of respiratory failure criteria. - PRISM-III. - Analytical parameters (leukocyte count, CRP, PCT). - Aetiological study in biological samples collected. - Antibiotic treatment received. - Final diagnosis
**Respiratory**	- Need and type of mechanical ventilation (invasive/non-invasive) - Duration of mechanical ventilation - Respiratory pattern (obstructive/restrictive) - Lung compliance and resistance values (if invasive ventilation) - Radiological findings (if CXR performed)
**Ultrasound**	- Presence of A and/or B lines. - Presence of lung sliding. - Presence and description of pulmonary consolidations. - Presence of air bronchogram (position/type). - Assessment of the pleural space (free/fluid occupancy). - Presence of pneumothorax.
**SWE**	- Lung elastance values (KPa and m/s) in liver, healthy lung and in pulmonary condensation - Quantification of microvascularization through SMI (ratio) in healthy lung and in lung consolidation.

PICU: Paediatric Intensive Care Unit; PRISM-III: Paediatric Risk of Mortality; CRP: C-reactive protein; PCT: procalcitonin; CXR: Chest X-ray; SWE: Shear Wave Elastography; SMI: Superb Microvascular Imaging.

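### Group 1 is labelled BTS/CDC-defined, but the criteria listed in Section 2.1 depart from the protocol's own account of those standards, leave one type of pneumonia uncovered, and use a blood item that differs between the two groups

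*Protocol article*

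**What the plan says.** **Named standard.** Section 2.1 (Study Design): "The final BP diagnosis will be made by a clinical expert using the BTS definition for CAP and the CDC criteria for VAP". The next sentence says what this comprises: compatible symptoms, abnormal auscultation, ultrasound findings as set out in Section 2.4.1, and blood abnormalities (raised leukocytes or neutrophils, CRP above 50 mg/L, and/or PCT above 1 ng/mL). For telling the two entities apart, "respiratory sample cultures will not be considered".

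**Atelectasis.** The same paragraph asks for respiratory distress, a child "without blood test abnormalities suggestive of bacterial infection (CRP < 50 mg/L and PCT < 1 ng/mL"), compatible ultrasound findings, and resolution after more ventilatory support and physiotherapy.

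**How the protocol describes the standards.** The Introduction says that the BTS "recommends basing the diagnosis on clinical findings alone, advising against routine use of chest X-rays (CXRs) to reduce radiation exposure". It says that VAP is "identified by the presence of a new infiltrate on CXR, along with positive microbiological findings from the lower respiratory tract", and/or two or more clinical signs. The following sentence calls the CDC criteria the most widely accepted. On nosocomial pneumonia: "This category includes both hospital-acquired pneumonia and ventilator-associated pneumonia (VAP").

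**Who is recruited and what is recorded.** Section 2.3 admits to Phase 2 children whose consolidation is present at PICU admission or arises later in the stay, with no requirement for ventilation. Table 2 lists "Analytical parameters (leukocyte count, CRP, PCT") and records radiological findings only where an X-ray was done.

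**The concern.** The BP and atelectasis labels are the reference for every between-group result in the study: the fourth outcome in Section 2.2, the cut-off meant to follow from it, and the ANOVA with Tukey comparisons in Section 2.7. The rule that produces the labels should therefore give one answer for each child.

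Section 2.1 names two external standards and then lists elements that differ from the protocol's own description of them, without saying which takes precedence. An expert who follows the named standards and one who follows the list can assign some children differently. The report could also describe Group 1 as BTS/CDC-defined pneumonia when the rule applied was something else. Separately, the same phrase about blood abnormalities is spelled out in two ways in one paragraph, so the blood item fails to separate the groups for one kind of child.

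**Working it through.** The check is mainly a comparison of text, with one small count.

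**Step 1. The plan's own figure.** Section 2.7 gives 53 per group. A one-way ANOVA with 3 groups, effect size 0.25 taken as Cohen's f, alpha 0.05 and power 80% needs a total of 157.19, that is 157.19 / 3 = 52.40 per group, rounded up to 53 (power 80.5% at 53). The figure reproduces and is not disputed. It takes the group labels as given.

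**Step 2. Named standards against the listed elements.**

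- *Community-acquired pneumonia.* Introduction: BTS rests on clinical findings alone. Section 2.1: clinical findings plus ultrasound plus blood markers. The basis differs.
- *VAP.* Introduction: a new X-ray infiltrate, plus lower-tract microbiology and/or two or more clinical signs. Section 2.1: no X-ray infiltrate; ultrasound and blood markers instead; cultures set aside. Table 2: X-ray findings only if one was taken. The infiltrate required by the description is neither in the list nor always collected.
- *Hospital-acquired pneumonia without ventilation.* The Introduction recognises it, Section 2.3 can recruit it, and Section 2.1 names no standard for it.

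An illustration of why precedence matters: take a ventilated child with respiratory distress, a new X-ray infiltrate and two clinical signs, whose leukocytes and neutrophils are normal, whose CRP and PCT are below the cut-offs, and whose air bronchogram is static. The Introduction's VAP description is met. Section 2.1's BP list is not met if its elements are read as jointly required. If the finding resolves with support and physiotherapy, the child meets the atelectasis criteria.

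**Step 3. The blood item in the two groups.** Code three yes/no indicators: L (leukocytosis or neutrophilia), C (CRP above 50), P (PCT above 1). Read the and/or in the BP list as any one being enough, and set aside values exactly at a cut-off. There are 2 × 2 × 2 = 8 combinations.

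- BP blood item met (L or C or P): 8 − 1 = 7.
- Atelectasis bracket met (not C and not P, L free): 2.
- Both met (L, not C, not P): 1. Check: 7 + 2 − 1 = 8.

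A child with leukocytosis, CRP 20 mg/L and PCT 0.3 ng/mL is in that one combination. With one meaning in both groups the overlap is 0, whichever markers are chosen: if L counts in both, atelectasis keeps only the all-negative combination; if L counts in neither, the two rules are exact complements on C and P.

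These are logical combinations, not patient frequencies.

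**Step 4. Can the item be verified?** Neutrophilia is a listed BP marker. Table 2 lists the leukocyte count, CRP and PCT, but no neutrophil count.

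**The case against.** Much can be said for the protocol.

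- *BTS.* Section 1 reports that the BTS discourages routine CRP and PCT for separating bacterial from viral disease, which is not the contrast studied here, and that the IDSA accepts these markers alongside clinical parameters in severe infection requiring hospitalization. Community-acquired pneumonia may also be viral, so the list may be meant to move from pneumonia to bacterial pneumonia. This stands in part: the BTS mismatch lies in the basis of diagnosis (clinical findings alone against clinical findings plus ultrasound and bloods), not in a ban on markers. A reader might also infer that any community-acquired case with CRP below 50 drops out of the list. It does not, because leukocytosis, neutrophilia or a PCT above 1 would satisfy the blood item.
- *VAP.* A reader might infer that setting cultures aside makes the VAP criteria impossible to meet. The and/or in the Introduction leaves a route through clinical signs, so only one route closes. Nor does the Introduction expressly attribute its description to the CDC. The mismatch between X-ray and ultrasound remains.
- *Uncovered category.* The listed elements could be applied to hospital-acquired pneumonia without ventilation. The gap is a missing named standard and does not by itself give a child two labels.
- *Blood item.* A reader might infer that the ultrasound pattern alone decides the overlapping cases. Section 2.1 also lists symptoms and auscultation for BP and resolution for atelectasis, so several other elements help.
- *Table 2* belongs to a condensed article, and the full data form may hold a differential count. That is a reason to confirm the field, not to assert that it is missing.
- *Expert judgement.* A clinical expert will settle many cases sensibly. But the text directs that expert to standards that the protocol describes differently from the list.

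**Conclusion.** The point holds in a limited form. Section 2.1 gives a group-defining rule that departs from the protocol's own description of the standards it names, does not say which prevails, names no standard for hospital-acquired pneumonia without ventilation, and gives the blood item a wider meaning for BP than for atelectasis. This goes beyond detail left to a fuller document, because the rule is stated here and is inconsistent as stated.

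The size cannot be put in patient terms. The overlap is one of eight marker combinations, assuming that any single marker satisfies the BP item, and the documents do not say how common that combination is. A reader might want to translate the ambiguity into a loss of AUC. The documents do not support this: they give no error rate, Section 2.7 names no AUC analysis, and the ambiguity would act systematically through the rule the expert follows, not as random label swapping.

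No judgement is made here on which clinical criteria are right. The problem is worth correcting before classification begins, but it does not invalidate the design.

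**What to change.** 1. Reconcile the Introduction with Sections 2.1 and 2.3 by stating one operative study definition of BP that covers every Phase 2 consolidation: community-acquired, hospital-acquired without ventilation, and ventilator-associated. Say explicitly whether the named standards or the list prevail, and what role X-ray findings have.
2. Do not describe Group 1 as BTS/CDC-defined where the operative definition departs from those standards.
3. Give the blood item the same meaning in both groups. The sponsor chooses the markers.
4. Make sure that every marker used is a collected variable. If neutrophilia stays, confirm or add the neutrophil count in Table 2.
5. Record acquisition type for each Phase 2 child.
6. As a sensitivity analysis, report the BP-atelectasis contrast without children who meet the blood item of both groups as now worded (leukocytosis or neutrophilia with CRP below 50 mg/L and PCT below 1 ng/mL).

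The cost is protocol wording, at most two data fields (neutrophil count and acquisition type) and one extra analysis on data already held. The downside is that the BTS/CDC label is given up or qualified.

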Given all this, in daily clinical practice, particularly in hospital wards or the PICU, the main difficulty for clinicians lies in the differentiation between BP and atelectasis, due to the similarity of their LUS findings in patients with possible similar clinical features. This is especially relevant in situations where BP has minimal impact and no fever or signs of infection are present during the patient’s physical examination. In contrast, VP is usually well differentiated through LUS and the clinical context, as are other conditions such as contusion or pulmonary thromboembolism, which can also cause lung consolidations but are typically framed within a very specific and characteristic clinical context.

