#### 2.4.1. Lung Ultrasound Imaging Acquisition

LUS evaluation will be performed at the bedside, adhering to standard clinical practice. Lung consolidation will be identified by liver-like images or parenchymal images within the lung tissue with dynamic or non-dynamic bronchogram, anfractuous edges, and “shred” signs.

The LUS findings of BP include:Disruption of the pleural lineHypoechoic consolidation with dynamic and arborizing air bronchogramPerilesional B-line enhancements.

The LUS findings of atelectasis include:Hypoechoic consolidation with non-dynamic and parallel air bronchogramPossible loss of pleural movement adjacent to the consolidation.

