## 4. Discussion

Pulmonary pathology is highly prevalent in paediatrics, especially in the PICU setting. The differential diagnosis between various pulmonary conditions, such as BP and atelectasis, is crucial to provide the best therapy approach for each patient, limiting antibiotic use to those who truly need it, thus preventing overexposure to antibiotics and the rise of antimicrobial resistance. Currently, the differential diagnosis requires invasive procedures such as analytical extractions and imaging tests like CXR, which involve a high radiation burden. In this regard, bedside LUS has been widely introduced into daily clinical practice in recent years, and our research group has published several studies on its application in paediatrics and its impact on the etiological approach and therapeutic decision-making. In the study by Haakma et al., conducted in an adult ICU, it was concluded that the presence of dynamic air bronchogram in LUS exhibited a sensitivity of 45% (95% CI, 31–60%) and a specificity of 99% (95% CI, 92–100%) for BP diagnosis, while the presence of Colour Doppler imaging demonstrated a sensitivity of 90% (95% CI, 79–97%) and a specificity of 68% (95% CI, 56–79%) [11]. Therefore, there remains an opportunity to improve the diagnosis of BP and other causes of pulmonary consolidation through quantifiable and non-invasive biomarkers.

In this context, through this study protocol, we propose the investigation of new quantifiable and reproducible imaging biomarkers that provide individualized results and can be obtained non-invasively, aiming to improve the quality of care with a gender perspective and focused on the well-being of the patient and their family. Specifically, we suggest studying lung elastance measured by SWE and microvascularization ratio measured by SMI. The incorporation of these new techniques would represent a significant change in the diagnostic approach for patients with BP and atelectasis [32,33,34].

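### The BP and atelectasis definitions leave children with mixed findings without a group, so the cut-off may rest on clear-cut cases only

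*Protocol article*

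**What the plan says.** Phase 2 (Sections 2.1 and 2.3) recruits PICU children with any lung consolidation confirmed by lung ultrasound (LUS) and then places them in one of two groups. No third or indeterminate group is named.

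- **BP.** "The final BP diagnosis will be made by a clinical expert using the BTS definition for CAP and the CDC criteria for VAP". The diagnosis is said to include compatible symptoms, abnormal auscultation, "LUS findings (according to Section 2.4.1), and blood test abnormalities suggestive of bacterial infection". The blood abnormalities listed are leukocytosis, neutrophilia, CRP above 50 mg/L and/or PCT above 1 ng/mL.
- **Atelectasis.** The child has respiratory distress. On the laboratory side the child must be "without blood test abnormalities suggestive of bacterial infection (CRP < 50 mg/L and PCT < 1 ng/mL"). For the imaging and the later course, the same sentence asks for "compatible LUS findings (according to Section 2.4.1), which resolve after increasing ventilatory support and performing respiratory physiotherapy".
- **LUS patterns.** Section 2.4.1 gives for BP a "consolidation with dynamic and arborizing air" bronchogram, with pleural line disruption and more B-lines around the lesion. For atelectasis it gives a non-dynamic, parallel bronchogram, possibly with loss of pleural movement.

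The Introduction places the clinical difficulty in BP and atelectasis looking alike on LUS, and adds: "This is especially relevant in situations where BP has minimal impact and no fever or signs of infection are present". Section 2.2 lists the BP versus atelectasis comparison as an outcome, leading to a cut-off. The Discussion suggests that SWE and SMI could complement LUS.

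**The concern.** The study is motivated by children whose LUS picture does not settle the diagnosis. Its two diagnostic labels are built from a typical LUS pattern together with concordant blood results. A child whose LUS and blood results disagree matches neither label, and the article does not say what happens to that child.

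Three things are at stake.

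- **The cut-off.** If mixed cases drop out, SWE and SMI are compared between typical BP and typical atelectasis. Contrasts and accuracy from such a set are usually better than in the unclear cases where the test would be used (spectrum bias).
- **The role beside LUS.** LUS pattern helps to define the groups, so LUS agrees with the reference partly by construction. These data cannot fairly show what SWE and SMI add to it.
- **The label.** The Introduction reports that "the British Thoracic Society (BTS) recommends basing the diagnosis on clinical findings alone" and that BTS discourages routine acute phase reactants. Section 2.1 nevertheless invokes the BTS definition and then lists CRP and PCT among its contents.

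**Working it through.** **Step 1. Run typical and mixed profiles through Sections 2.1 and 2.4.1, taking each listed component as needed.**

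| Bronchogram | Blood results | Resolves | BP | Atelectasis |
|---|---|---|---|---|
| Dynamic | CRP > 50 or PCT > 1 | – | fits | no |
| Static | CRP < 50, PCT < 1, normal counts | yes | no | fits |
| Static | CRP > 50 or PCT > 1 | either | no (LUS) | no (blood) |
| Dynamic | CRP < 50, PCT < 1, normal counts | either | no (blood) | no (LUS) |
| Static | CRP < 50, PCT < 1, normal counts | no | no | no (resolution) |

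The last three rows have no group. A CRP of exactly 50 or a PCT of exactly 1 is also outside both sets of limits.

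**Step 2. Overlap of the blood rules.** A child with leukocytosis or neutrophilia but CRP < 50 and PCT < 1 meets the BP blood component, because the list is joined by and/or. The same child meets the atelectasis bracket, which names only CRP and PCT. This overlap concerns the blood component, not the whole definition.

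**Step 3. Reproduce the plan's figure.** Inputs from Section 2.7: three groups, f = 0.25, alpha 0.05, power 80%. One-way ANOVA with the noncentral F distribution gives n = 52.40 per group, rounded up to 53. At n = 53 the noncentrality is 3 × 53 × 0.25² = 9.94 and power is 0.805. The stated 53 is right.

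**Step 4. Illustration of how many BP cases could be affected.** The Discussion cites an adult ICU study in which "the presence of dynamic air bronchogram in LUS exhibited a sensitivity of 45" per cent (95% CI 31–60%) for BP. Assume that this carries over to children and that the dynamic pattern is strictly required.

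- True BP without the pattern: 1 − 0.45 = 55% (1 − 0.60 = 40% to 1 − 0.31 = 69%).
- True BP needed for 53 classified: 53/0.45 = 117.8, so 118. Range: 53/0.60 = 88.3, so 89; 53/0.31 = 170.97, so 171.
- If instead only 53 true BP cases are recruited, the number classified is 53 × 0.45 = 23.9, about 24 (53 × 0.31 = 16.4 to 53 × 0.60 = 31.8, so 16 to 32).

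**Step 5. Power with the smaller BP group.** Put BP and atelectasis at ±d/2 and normal midway, with d = 0.25 × √6 = 0.612 SD, which gives f = 0.25 at equal group sizes. With 24, 53 and 53 children the weighted mean is (24 − 53) × 0.306/130 = −0.068. The noncentrality is 24 × 0.374² + 53 × 0.238² + 53 × 0.068² ≈ 6.61. ANOVA power is then about 0.62, with 0.53 at 16 BP cases and 0.69 at 32. The effect is held fixed here. A set of clear-cut cases may show a larger contrast, so the more lasting harm is to the cut-off.

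**The case against.** The strongest reply is that the definitions are not a strict checklist. A clinical expert makes the BP diagnosis, the components are given as what it includes, and nothing says that discordant children are excluded. Section 2.4.1 likewise lists typical findings without calling the dynamic bronchogram mandatory. This stands in part: the expert may well place mixed cases. But no rule says how, and only two groups exist, so the gap in the written definitions remains.

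The Introduction's hard cases lack fever or infection signs on physical examination. They may still have raised CRP or PCT and be classifiable later. That is fair: difficult at the bedside is not the same as outside both definitions, and only some of these children are affected.

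The numerical illustration is also open to challenge. It uses one sign from adults, while the Introduction cites a pooled paediatric LUS sensitivity of 0.95, which would give 53/0.95 = 55.8, or 56 children. That figure is for LUS as a whole, not for the bronchogram type, but it shows how far the count depends on the assumption. The leukocytosis overlap is thin too: it disappears if the bracket is read as examples of the wider phrase before it.

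A reader might infer more than the text supports:

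- **Incorporation of the index tests.** SWE and SMI appear in neither definition. LUS does, so the circularity affects comparison with LUS only.
- **One examiner for everything.** Section 3 states a single examiner for the biomarkers, not for LUS or the final diagnosis.
- **A conflict between the CDC criteria and setting cultures aside.** The Introduction describes VAP as a new infiltrate with positive microbiology and/or clinical signs, so on the article's own account cultures are not indispensable.
- **Failure of a listed outcome.** Added value over LUS is a possibility raised in the Discussion, not an outcome in Section 2.2.

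**Conclusion.** The concern holds in limited form. As written, the two definitions do not cover all recruited children, and their blood criteria may overlap. If discordant children are left out, the BP versus atelectasis contrast and the cut-off will look too accurate for unclear cases. The comparison in clear-cut cases remains estimable, but these data cannot fairly support a complementary role to LUS.

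The size of the accuracy inflation cannot be derived from the article. The figure of 118 (89–171) true BP cases for 53 classified, and the fall in power from 0.80 to about 0.62 (0.53–0.69) if only 53 true cases are recruited, are alternative illustrations. Both assume that the adult sensitivity applies and that the pattern is strictly required.

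The reference to the BTS definition is in tension with the article's own account of BTS and needs reconciling. The change is worth making before analysis, but the point does not invalidate the study.

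**What to change.** 1. Keep every recruited child with consolidation in the analysis. Report those who meet neither or both definitions as an indeterminate stratum, and repeat the group comparison and the cut-off accuracy with all of them assigned to BP and then all to atelectasis.
2. Add a sensitivity analysis with a reference diagnosis that uses LUS only to confirm consolidation, not bronchogram type. Such a rule leans more on CRP and PCT, with its own misclassification risk, so it is better placed beside the current rule than in its stead.
3. Have the expert assign the final diagnosis with the SWE and SMI values hidden. A full protocol may already provide for this; if so, the article need only say it.
4. Word the blood criteria of the two groups so that they are mutually exclusive, including values on the limits. The investigators choose the limits; this concerns the research label, not patient care. Reconcile the BTS reference with the Introduction, for example by calling the rule a study-specific composite.

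The cost is protocol wording, restricted database fields and a few extra analyses, with no extra patients or staff. Reported accuracy will probably be lower.
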